## Abstract

**Background:**

Smoke-free housing policies in multiunit housing are increasingly widespread interventions to reduce smoking and secondhand smoke exposure. Little research has identified factors that impede compliance with smoke-free housing policies in low-income multiunit housing and test corresponding solutions.

**Methods:**

We are using an experimental design to test two compliance support interventions: (A) a “compliance through reduction (via relocation and reduction in personal smoking) and cessation” intervention targets households with smokers and involves support to shift smoking practices to designated areas, reduce personal smoking, and deliver in-residence smoking cessation support services via trained peer educators and (B) a “compliance through resident endorsement” intervention involving voluntary adoption of smoke-free living environments through personal pledges, visible door markers and/or via social media. We will compare randomly sampled participants in buildings that receive A or B or A plus B to the NYCHA standard approach,

**Discussion:**

This RCT addresses key gaps in knowledge and capitalizes on key scientific opportunities by: 1) leveraging the federal mandate to ban smoking in a public housing system of more than sufficient size to conduct an adequately powered RCT; 2) expanding our understanding of smoke-free policy compliance beyond policy implementation by testing two novel treatments: a) in-residence smoking cessation and b) resident endorsement, while 3) addressing population and location-specific tobacco-related disparities. At the conclusion of the study, this RCT will have leveraged a monumental policy shift affecting nearly half a million NYC public housing residents, many of whom disproportionately experience chronic illness and are more likely to smoke and be exposed to secondhand smoke than other city residents. This first-ever RCT will test the effects of much-needed compliance strategies on resident smoking behavior and secondhand smoke exposure in multiunit housing.

**Trial registration::**

Clinical Trials Registered, NCT05016505

## Introduction

### Background And Rationale {6a}

SPIRIT guidance: Description of research question and justification for undertaking the trial, including summary of relevant studies (published and unpublished) examining benefits and harms for each intervention.

Tobacco use remains a public health priority, especially for racial/ethnic minorities and low-income populations (1). Evidence demonstrating the adverse health effects of smoking has led to comprehensive tobacco control policies including smoking bans in public venues (2). Such bans provide protection from secondhand smoke, reduce smoking overall, and increase adoption of voluntary smoke-free rules in private homes (3–6), producing positive health effects, most notably in reducing asthma (7). Prior to the pandemic, Americans spent, on average, 69% of their time at home (8), which has increased with the emphasis on staying home during the pandemic. Considering this, housing represents a major potential source of secondhand smoke exposure, and is, in fact, the largest source of secondhand smoke exposure for children (9). Approaches to limit the spread of secondhand smoke in indoor spaces–such as separation of smokers and nonsmokers, ventilation, or cleaning the air–cannot fully eliminate exposure (10, 11). Building-wide bans on indoor smoking go further to achieve this goal.

Individuals’ private homes have traditionally been considered outside the scope of appropriate smoking regulations (12). However, the case for smoke-free housing has been made convincingly enough (13–15) to prompt the United States Department of Housing and Urban Development (HUD) to mandate that all public housing developments adopt such policies (16). These policies carry potential economic, environmental, and health benefits to residents and owners (17), particularly in multiunit housing.

It should be noted that disadvantaged groups are likely to live in multiunit housing where residents have reported higher smoking (18) and exposure to secondhand tobacco smoke largely due to air exchange between apartments through mechanisms such as ventilation systems, common areas, and contiguous party walls (17, 19). In fact, an estimated 28 million multiunit housing residents with smoke-free rules in their unit experience secondhand smoke exposure each year (20); and secondhand smoke incursions into resident units are noted whether measured by self-reports, environmental markers, or biomarkers (21–23).

Moreover, in a key study, 89% of non-smoking households were exposed to secondhand smoke resulting in involuntary smoking activity as high as one cigarette per day (24–28). Non-smoking multiunit housing residents, both adults and children, exhibited significantly elevated levels of cotinine, a biomarker of cigarette smoke exposure (21, 24–28), compared to non-smokers living in detached homes (26, 29). Similarly, 84.5% of children living in apartments without any household members who smoked inside “had a cotinine level that indicated recent tobacco-smoke exposure.” One cause for this finding is the seepage through ventilation systems or walls from neighboring apartments where smoking took place (19, 30–35). These studies all conclude that smoke-free housing policies involving building-wide bans on indoor smoking would effectively reduce secondhand smoke exposure (19, 21, 31–35, 23–30).

Early studies of smoke-free housing policies have shown some protections from smoking hazards for smokers and non-smokers alike through decreased indoor secondhand smoke exposure, decreased smoking overall, and increased quit attempts (22, 24–28). Yet, compliance with smoke-free housing policies is not assured (21). For example, one study found that about half of residents or their guests had violated the policy (29). In one study, almost 20% of residents reported “frequent exposure” to secondhand smoke after smoke-free housing policy implementation (26), and non-smoker residents still frequently experience secondhand smoke incursions (19, 30–35). Another study found that though there were reductions in environmental markers of secondhand smoke initially, there was a 33% increase post 12 months of the policy being implemented (36) while another study found no change 12 months post implementation (37).

[name] (PI) explored the multifaceted reasons for non-compliance, captured in the ‘social contract of smoke-free housing’ concept which describes factors such as social ties and bi-directional rights and obligations between residents and property management that play a role in compliance (38). A study assessing resident opinions on the smoke-free policy prior to implementation found 65% of residents supported the policy (39). However, residents also expressed expectations of poor policy compliance due to lack of enforcement, safety concerns/inconvenience with smoking relocation, and general discontent with their housing authority and/or living conditions (39–41). Such concerns also remain consistent post policy implementation (42, 43). A mixed methods study focusing on resident experiences pre and post policy implementation found residents still reported smoking violations 1 year after the policy was implemented. Participants in the study reported that the policy overreached by telling people what to do, was inconsistently enforced, and created the perception that smokers were being unfairly targeted given that other pressing housing issues were not addressed (42). Support for the policy remained unchanged for the study highlighting residents’ willingness to accept the policy, but the finding of a decline in satisfaction with enforcement indicated a need to address contextual barriers to compliance (42). Continued exposure to secondhand smoke further poses a threat to overall satisfaction of housing with those with continued secondhand smoke exposure reporting lower satisfaction of housing conditions when repairs and improvements are made (44). Further, it was found that compliance is often realized in an effort to avoid punishment rather than a genuine wish to comply and that receiving support as opposed to penalization is essential (40). A Detroit based study found that though some public housing residents had a desire to quit, limited cessation services, lack of access to medications, and social triggers made it difficult (45). Another study found that 48.6% of 233 cigarette smokers thought about quitting specifically in response to the policy 12 months post implementation (46). Overall, these studies demonstrate a general consensus that providing smoking cessation services would be beneficial in supporting compliance to the smoke-free mandate. Further evidence suggests that consistent engagement of residents in the process of implementation could support increased compliance (36, 42–44, 47). Though these strategies have been suggested, no study to date provides a comprehensive understanding and testing of effective compliance support strategies for smoke-free policies.

The proposed Randomized Control Trial (RCT) addresses key gaps in knowledge and capitalizes on unique scientific opportunities that: 1) leverage the HUD smoking ban within a large public housing system that will enable an adequately powered RCT; 2) expand understanding beyond smoke-free policy implementation to focus on compliance and effectiveness, and 3) address population and location-specific tobacco disparities.

### Objectives {7}

The broad objective of this study is to use an experimental design to test two smoke-free policy compliance support interventions: (A) a “compliance through reduction (via relocation and reduction in personal smoking) and cessation” intervention targets households with smokers and involves support to shift smoking practices to designated areas and reducing personal smoking, and deliver in-residence smoking cessation support services via trained peer educators and (B) a “compliance through resident endorsement” intervention involving voluntary adoption of smoke-free living environments through personal pledges, visible door markers and/or via social media. We will compare randomly sampled participants in buildings that receive A or B or A plus B to the NYCHA standard approach.

We seek to achieve the following specific aims:

Aim 1: Experimentally test if compliance support interventions reduce personal smoking behavior.

Aim 2: Experimentally test if compliance support interventions reduce secondhand smoke exposure.

Aim 3: Determine if the tobacco retail environment surrounding each building moderates the relationship between compliance support interventions and smoking-related outcomes.

We hypothesize that the reduction/cessation plus resident endorsement intervention will yield significantly larger reductions in personal smoking and second-hand smoke exposure, compared to standalone interventions and the standard approach.

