### Outcomes {12}

#### Primary Outcomes:

There are three primary outcomes being measured:

We will evaluate the change in number of cigarettes smoked per day using self-reported average number of cigarettes smoked per day among smokers measured at the time of baseline assessment, interim assessment (approximately 3 months post-intervention), and long-term assessment (approximately 12 months post intervention).We will evaluate change in salivary cotinine levels for 25% of the sample via passive drool collection among smokers and non-smokers collected at baseline assessment and the long-term assessment.We will evaluate change in secondhand smoke exposure via self-reported amount of exposure to secondhand smoke. This will be measured in all three assessments.

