#### Sample Size {14}

Power analysis was conducted using software PASS.15 for the primary outcome (change in salivary cotinine over a year) in Aims 1 and 2. Sampling 16 clusters (buildings) with 4 subjects per cluster (smokers for Aim 1, non-smokers for Aim 2) in each arm, we have 128 subjects per group or 256 in groups with or without a specific type of treatment (e.g. resident endorsement vs. no endorsement, cessation vs. no cessation). We calculated effect size as group mean difference in unit of standard deviation (SD) of the outcome, based on a two-sided test for mean difference between two groups in a cluster-randomized design with power of 80%. To compare groups with and without specific type of treatment, the group size of 256 may detect effect size of 0.283SD, 0.299SD, 0.312SD at significance level alpha = 0.05 for intra-cluster correlation coefficient r = 0.1, 0.15, 0.2, respectively. To compare intervention arms to the control arm, we have 3 comparisons and use conservative Bonferroni adjustment for multiple tests on significance level that alpha = 0.0167 (= 0.05/3). The sample size of 128 subject per arm may detect effect size of 0.472SD, 0.499SD and 0.524SD for r = 0.1, 0.15 and 0.2, respectively, at alpha = 0.0167. To put these numbers in perspective, using mean and SD estimated from a study of smokers in Maryland, an effect size of 0.283SD would correspond to a mean difference in salivary cotinine between the two intervention groups of 55.3 ng/mL with group SD = 195.4 ng/mL for smokers and of 0.19 ng/mL with group SD = 0.672 ng/mL for non-smokers.124 For instance a mean difference in 5 cigarettes smoked per day in the same study was 59.6 ng/mL for smokers.124 In England, following the smoke-free legislation salivary cotinine declined from mean level of 0.36 to 0.07 ng/mL (mean difference 0.29 ng/mL) among non-smokers.125 These findings support that we have sufficient power to estimate the impact of our interventions. The study is powered on an 80% retention rate, which we have achieved in other studies. Reasons for attrition will be tracked; those lost to follow up will be compared to the final sample.

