### Secondary outcome and Sensitivity analyses

1)

We will use GLMRM with logit or log links for binary or count outcomes, respectively, to evaluate group differences in the outcome changes from baseline to 3 and 12-month follow-up. The models will include predictors of dummy variables for time and group assignment as well as for group by time interaction as described above. Aim 1 (smoking behavior) secondary outcomes are whether smokers have successfully quit (binary), the mean number of quitting attempts (continuous). Aim 2 (exposure to secondhand smoke) secondary outcomes include ever observing someone smoking indoors within the building in the past 7 days (both smoker and non-smoker participants) (binary), hours of secondhand smoke exposure in the building in the past 7 days (count), number of people smoking and number of cigarette butts in common areas of the building (count).

Differential effect of the tobacco retail environment. The impact of differential tobacco retail environments (e.g., retailer density) around each building will be systematically evaluated for the primary outcomes and for quantitative secondary outcomes listed in Aims 1 and 2. The tobacco retail environment will be measured at the longitude-latitude point coordinate of each building using a geographic kernel density estimate with standard bandwidth to estimate the square mileage density of tobacco sellers in the surrounding area for each specific building point coordinate. This information is publicly available from the City of New York. As continuous metrics, these kernel density estimates will be separated in tertiles and at median breaks and the relationships tested in Aims 1 and 2 will then be tested within separate levels of tobacco retail density. We will also extend the GLMRM with identity or log link for each outcome variable in Aims 1 and 2 by adding the factor for retail environment, its interaction with group, time, and group by time interaction. In addition to the analysis for effect of a pre-specified modifier (the retail environment), we will conduct several a priori subgroup analyses to explore potential differential effect of the interventions in the continuous outcomes by age, sex, knowledge, and attitude towards the policy.

We will evaluate reliability of self-reported measures of active and passive smoking and revisit the primary analyses adjusting for potential imperfect reliability using regression calibration approaches.

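### The hypothesis needs A+B compared with A alone and with B alone; the plan names neither contrast, and it labels the primary outcome inconsistently

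*Protocol article*

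**What the plan says.** All references are to the protocol article.

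- **Hypothesis (Objectives {7}).** The combined intervention "will yield significantly larger reductions in personal smoking and second-hand smoke exposure, compared to standalone interventions and the standard approach". The same section also declares a comparison of buildings receiving A, B or A+B with the housing authority's standard approach.
- **Error control (Sample Size {14}).** "To compare intervention arms to the control arm, we have 3 comparisons and use conservative Bonferroni adjustment for multiple tests", with alpha 0.0167. The factorial margins (with versus without A, with versus without B) are powered at 0.05 with no adjustment. The calculation is made for a single primary outcome, the one-year change in salivary cotinine.
- **Model (Statistical methods, Primary outcome).** A four-arm repeated-measures model expresses each intervention arm's change as a difference from the reference arm at each of two follow-ups. A test of ßk1 = ßk2 + ßk3 decides whether a simpler additive model is used.
- **Arm numbering (Trial design {8}).** 1 = reduction/cessation (A), 2 = resident endorsement (B), 3 = both, 4 = standard approach.
- **Allocation (Sequence Generation {16a}).** 48 buildings are randomised among A, B and A+B. The 16 control buildings come from a separate list of sites that the housing authority picked for its own programme.
- **Outcomes (Outcomes {12}).** "There are three primary outcomes being measured": cigarettes per day, salivary cotinine and self-reported secondhand smoke exposure. The statistical section treats seven-day secondhand-smoke hours as primary and uses cotinine to check the reliability of self-report. The next section lists "hours of secondhand smoke exposure in the building in the past 7 days (count") among the secondary outcomes.

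**The concern.** The hypothesis has three contrasts: A+B against A, against B and against the standard approach. Only the last is in the adjusted family. With the other two unnamed, a reader may take a significant A+B versus control result beside a non-significant A versus control result as showing that A+B beats A. That pattern is not a test of the difference between A+B and A.

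The trial's main claim is about what the combination adds. The two missing contrasts are also the ones that lie wholly within the 48 randomised buildings, whereas every comparison with control crosses two separately drawn lists of buildings.

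The unsettled primary outcome adds to this. The Bonferroni divisor counts three arms for one outcome at one time. With three outcomes called primary, two of them measured at two follow-ups, it is unclear which result decides the trial.

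**Working it through.** **1. The plan's own figures.** Inputs from Sample Size {14}: two-sided test, 80% power, 128 per arm, clusters of 4, ICC 0.1, 0.15 and 0.2, alpha 0.05/3 = 0.0167.

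- Design effect = 1 + (4 − 1) × ICC = 1.30, 1.45, 1.60.
- SE in SD units = √(2 × design effect / 128) = 0.1425, 0.1505, 0.1581.
- Normal approximation: (2.394 + 0.842) × SE = 0.461, 0.487, 0.512.
- Non-central t with 62 df (32 clusters of 4 per arm): 0.472, 0.499, 0.524.

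The last line matches "The sample size of 128 subject per arm may detect effect size of 0.472SD, 0.499SD and 0.524SD". The arithmetic of the adjustment is therefore right. The mismatch lies in which three contrasts it counts.

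**2. Hypothesised contrasts against specified ones.**

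| Contrast | In hypothesis | In adjusted family |
|---|---|---|
| A+B vs control | yes | yes |
| A+B vs A | yes | no |
| A+B vs B | yes | no |
| A vs control | no | yes |
| B vs control | no | yes |

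**3. Whether the margins fill the gap.** With equal arms, the B margin = ½[(A+B − A) + (B − control)].

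- It equals A+B versus A only if the two bracketed terms are equal, which is additivity. Otherwise it is their average.
- The second term uses the separately drawn control buildings. The first does not.

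**4. Whether the additivity test supports the substitution.** Let A alone have effect a, B alone effect b, and suppose additivity holds. Under the Trial design numbering, ßk1 = a, ßk2 = b and ßk3 = a + b. The stated null then reads a = b + (a + b), that is b = 0. It is true under additivity only if B does nothing. The null is correct only if index 1 means the combined arm, which contradicts Trial design {8}.

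**5. Number of primary tests.** Cigarettes per day and self-reported exposure have two follow-ups each, and cotinine has one: 2 + 2 + 1 = 5 outcome-time pairs, counting cotinine once. Three arm-versus-control contrasts give 15 tests. Chance of at least one false positive if each is tested at 0.0167:

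- Independence: 1 − (1 − 0.0167)^15 = 0.22. Bonferroni bound: 15 × 0.0167 = 0.25.
- Simulation with the shared control arm: about 0.20 with uncorrelated outcome-time pairs and 0.14 with correlation 0.7. One outcome at one time gives 0.045.

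**6. What enlarging the family costs** (the plan's 128 per arm, non-central t with 62 df):

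| Family | Alpha | Detectable SD at ICC 0.1 / 0.15 / 0.2 |
|---|---|---|
| 3 contrasts | 0.0167 | 0.472 / 0.499 / 0.524 |
| 5 contrasts (all rows of the table in step 2) | 0.01 | 0.501 / 0.529 / 0.555 |

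**7. Power for the missing contrasts** (normal approximation, ICC 0.1, 128 per arm). As an illustration, suppose B adds 0.283 SD, the plan's own margin figure. Then 0.283/0.1425 = 1.986. Power for A+B versus A is Φ(1.986 − 1.960) = 51% at 0.05 and Φ(1.986 − 2.394) = 34% at 0.0167. If A+B must beat all three comparators and each true difference is 0.472 SD, simulated joint power is about 80% with each test at 0.05 and 64% at 0.0167.

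**The case against.** **The model can already answer the question.** The four-arm model has a coefficient for each arm at each follow-up, so A+B versus A and A+B versus B are differences of estimated coefficients. This stands. A reader might infer that the plan cannot confirm or refute its hypothesis. The documents do not support that, because the contrasts are unnamed but estimable.

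**Arm versus control is a declared comparison.** The Objectives section states it just before the hypothesis. This stands too, and it is a reason to keep those comparisons and not to demote them.

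**Alpha rules across outcomes and times may sit in an analysis plan that is not shown.** That is fair, so their absence is not the point. Such a plan would still have to reconcile sections that conflict on the primary outcome, and a hypothesis that conflicts with its stated family.

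**The hypothesis reads conjunctively.** If A+B must beat every comparator, no alpha split across contrasts is needed and joint power is the issue. The article does not say which reading applies.

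**Two larger numbers are tempting.** Three outcomes at two follow-ups would give 18 tests and 26%, but cotinine has only the 12-month follow-up. With 16 × 4 = 64 participants per arm for each aim, the detectable difference would be 0.685, 0.724 and 0.760 SD. That comes from a separate discrepancy between 64 and 128 in Sample Size {14}. Swapping one three-contrast family for another with equal arms leaves 0.472, 0.499 and 0.524 unchanged.

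**Conclusion.** The point holds in limited form and should be corrected. Two of the three hypothesised contrasts are never specified as tests. The margins are a substitute only under additivity, they bring in separately drawn controls, and the additivity null contradicts the arm numbering. Four sections give incompatible accounts of the primary outcome.

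The false-positive figure of about 22% assumes 15 independent tests, each at 0.0167, with no further rule in an unseen analysis plan. Correlation lowers it, to about 14% in the simulation with correlation 0.7. The detectable differences and power figures take the plan's 128 per arm at face value, before the 25% cotinine subsample and 80% retention. The contradictions between sections do not depend on any of these assumptions.

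**What to change.** 1. Add A+B versus A and A+B versus B, by arm name and not by coefficient index, as pre-specified linear contrasts from the existing four-arm model at a named primary time point (for example 12 months). State that they will not be inferred from separate arm-versus-control results.
2. Keep the three arm-versus-control comparisons.
3. State the success rule. If all contrasts must succeed, use no alpha split and report joint power. If any one suffices, apply Holm or Bonferroni over the enlarged family and state the detectable difference.
4. Rewrite the additivity null to fit Trial design {8}: combined-arm effect = A effect + B effect.
5. Name one primary outcome per aim, make Outcomes {12}, Sample Size {14} and the statistical sections agree, and list seven-day secondhand-smoke hours only once.

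The cost is wording and no new data. With five contrasts at alpha 0.01, the stated detectable difference becomes 0.501, 0.529 and 0.555 SD in place of 0.472, 0.499 and 0.524. The change should be dated before outcome comparisons by arm are seen, since Interim Analyses {21b} has the research team assessing preliminary results.
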